## Methods

The aims of this study are to determine the feasibility of implementing the *Bundle* in residential aged care homes and to determine the utility and feasibility of a definitive phase III trial to assess its effectiveness. The aims are encompassed by the following five objectives:To determine the acceptability of the *Bundle* to end users in residential aged care homes.To explore the fidelity of the implementation of the *Bundle*.To investigate the compatibility of the *Bundle* with current catheter care practices, procedures and policies.To investigate the internal consistency, construct validity and convergent validity of a scale developed to measure nurses’ knowledge and confidence to provide person-centred IDC care.To gather descriptive pilot data related to rates of IDC-related complications, and staff knowledge and confidence to provide person-centred IDC care.

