### Intervention

Participants (managers/senior leaders, nurses, and PCWs) at intervention sites will access all elements of the *Bundle*. The *Bundle* will be implemented in two consecutive phases, (1) education phase and (2) application to practice phase.

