t_0_, t_1_	X	X	IDC-IMPROVE Clinical Data Extraction Form	Clinical information about age range, gender, IDC type, reason for IDC, duration of IDC, number of IDC changes, disciplinary background of staff who perform the change, number and type of IDC-related complications, and number of admissions to hospital and emergency departments for IDC-related complications for residents with an IDC for the prior 3 months, to be completed by managers/senior leaders or RNs
Feasibility and sustainability data collection tools				
t_0_, t_2_	X	X	IDC-IMPROVE Catheter Care Audit Tool	A pre and post intervention audit of each aged care home, IDC-related organisational policies and practices, to be completed by managers/senior leaders and administered with the aged care home demographic survey
t_0_, t_1_, t_2_	X		Participant Completion and Withdrawal Record	Number of nurses and PCWs who enrol, complete or withdraw from the education or application to practice phase
t_1_	X		Online Catheter Care Course for Nurses Feedback Survey	Rating scale to capture nurses’ satisfaction with the content and questions on their experience of the course
t_1_	X		Catheterisation Skills Workshop Feedback Survey	An online survey nurses will be asked to complete at the end of the catheterisation skills workshop
t_2_	X		Semi-structured qualitative interviews	Interviews will be conducted with nurses, PCWs and managers exploring participants’ perspectives and experiences with the *Bundle*, barriers and enablers to implementing the trial, contextual factors affecting IDC care and implementation of the *Bundle*

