**Table 2 Tab2:**
[figure not shown]
Timeline of study procedures, including enrolment, interventions, and assessment points

**Table 3 Tab3:** Criteria, data collection methods, and thresholds for progression to a definitive trial

Criteria	Data collection	Threshold
(ii) Acceptability of the bundle	• Feedback surveys • Audit tool • Qualitative interviews	• 75% + participants “satisfied” or “very satisfied” • Thematic analysis of qualitative interviews • Descriptive analysis of audit tool
(iii) Fidelity of implementation	• Participant completion and withdrawal record • KCS-Nurse • KCS-PCW • NPC-Scale-SF • Clinical data extraction form	• Site retention: 20 sites complete all trial phases • Participant retention: ≥ 80% of enrolled participants complete all study follow-ups (t_0_, t_1_, t_2_) • Fidelity to data collection: 75% of all *expected* data points collected across KCS-Nurse, KCS-PCW, NPC-Scale-SF, and Clinical Data Extraction Forms from sites and participants who complete all trial phases • Internal Consistency of KCS-Nurse: Achieves acceptable internal consistency
(iv) Compatibility of bundle with standard practice	• Qualitative interviews • Audit tool	• Thematic analysis of qualitative interviews • Descriptive analysis of audit tool

Prior to site randomisation, information will be collected from organisations on their size, ownership and staffing, and from individual nurses and PCWs in terms of their qualifications, years in nursing and in working in residential aged care. The research team will provide sites with extraction forms to obtain key information from the medical records of residents with IDCs who consent to participate in the study. Research staff will be trained in obtaining informed consent and in the use of the extraction forms prior to inviting residents to participate. We anticipate some participating nurses may complete the online course but will be unable to complete a workshop due to workshop capacity limitations. These nurses will be flagged, and their outcome data will not be combined with workshop participants’ data.

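### The 75% satisfaction threshold is labelled as participants' acceptability of the Bundle, but the listed surveys can supply only nurses' ratings of the online course and the workshop

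*Protocol article*

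**What the plan says.** The first objective in Methods is to establish how acceptable the Bundle is "to end users in residential aged care homes". Acceptability is then one of three parts of the composite primary outcome.

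The Intervention section states who the participants are: "Participants (managers/senior leaders, nurses, and PCWs) at intervention sites will access all elements of the" Bundle.

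The acceptability row of Table 3 names three data sources: feedback surveys, the audit tool and qualitative interviews. Only one entry in its threshold column is a number: "75% + participants “satisfied” or “very satisfied". The other two entries name a type of analysis, thematic for the interviews and descriptive for the audit.

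Table 1 lists the instruments and their target groups. Its two feedback surveys are both at t1 and in the intervention arm only:

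- Nurses' online course survey: "Rating scale to capture nurses’ satisfaction with the content and questions on their experience of the course".
- Workshop survey: "An online survey nurses will be asked to complete at the end of the catheterisation skills workshop".

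The other two sources in the acceptability row are also described there. For the t2 interviews: "Interviews will be conducted with nurses, PCWs and managers exploring participants’ perspectives and experiences with the" Bundle. For the audit tool: "to be completed by managers/senior leaders and administered with the aged care home demographic survey".

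**The concern.** The threshold and the instruments that feed it do not match. The criterion is worded for all participants and for the Bundle as a whole. The ratings that can be set against it come from one of three staff groups and concern two of the things delivered.

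The 75% is the only acceptability figure that can be met or missed, so it is the one a progression report is likely to quote. Reported as worded, a pass would read as satisfaction among managers, nurses and PCWs with the whole intervention, although two of these groups were never asked for a rating. A later analysis plan could settle a denominator, but it could not supply ratings that were not collected.

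**Working it through.** **The plan's own calculated figure.** The only sample size in the article is 62 nurses, for estimating an 80% completion rate to within 10 points. It reproduces: n = 1.96² × 0.80 × 0.20 / 0.10² = 61.5, rounded up to 62. It concerns completion, not satisfaction, and is not in dispute. The point here rests on reading the tables together, and the arithmetic only sizes it.

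**Step 1: which delivered elements have a satisfaction rating.**

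| Element | Staff group | Satisfaction survey in Table 1 |
|---|---|---|
| Online course for nurses | Nurses | Yes, t1 |
| Catheterisation skills workshop | Nurses | Feedback survey, t1 |
| Online course for PCWs | PCWs | None |
| Toolkit | Managers/senior leaders | None |
| Phase 2 coaching | Nurses, managers/senior leaders | None |

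The workshop survey is answered when the workshop ends, and Phase 2 follows the course and workshop, so that survey cannot rate the coaching. The course survey is described as concerning the course, so it does not rate the coaching either, wherever t1 falls.

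**Step 2: planned staff in the 12 intervention homes.**

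- Nurses: four per site (Nurses subsection, 96 in total), so 12 × 4 = 48. Four is stated as a minimum, and 48 is the figure implied by the planned total.
- PCWs: 100 over both arms (Personal care workers subsection). The split is not stated. I assume an even one, 50, with a range of 40 to 60.
- Managers/senior leaders: one to two per site, so 12 to 24.

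**Step 3: share that can enter the 75%.**

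- Total with 50 PCWs: 48 + 50 + 12 = 110, up to 48 + 50 + 24 = 122.
- Share: 48/122 = 39%, up to 48/110 = 44%.
- With 40 to 60 PCWs, the extremes are 48/(48 + 60 + 24) = 48/132 = 36% and 48/(48 + 40 + 12) = 48/100 = 48%.

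**Step 4: what a pass could rest on.** Suppose every one of the 48 nurses answers. Then 36 satisfied nurses meet the threshold, since 36/48 = 75%. That is 36/122 = 30% to 36/110 = 33% of planned intervention staff. The other 62 to 74 people (110 − 48 and 122 − 48) have given no rating in either direction.

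**The case against.** The strongest reply is that this is a mixed-methods feasibility study and the surveys do not decide acceptability alone. The same Table 3 row includes interviews with nurses, PCWs and managers about the Bundle, and the managers' audit. The process evaluation brings these together, and a missed threshold does not automatically stop progression. This stands, and it rules out the reading that PCWs and managers do not count towards acceptability. They count, but without a cut-off, and the audit concerns organisational policies and practices rather than satisfaction. The mismatch in the numeric criterion remains.

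A reader might also infer that the percentage leaves out nurses who abandon the Bundle and so leans towards a pass. The document does not establish this. The workshop survey by its nature reaches only attenders, but the course survey is placed at t1 with no condition that the course be finished, and a nurse without a workshop place can still answer it. Withdrawals are recorded separately and feed the criterion that at least 80% of enrolled participants complete follow-up.

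The base of the 75% and the handling of non-response may be set out in an analysis plan or full protocol that is not shown, so their absence is not a fault here.

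Finally, Table 2 is not visible. It is described as giving timepoints, while Table 1 is presented as the list of instruments and target groups, so a further survey appearing only in Table 2 is unlikely but cannot be excluded.

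**Conclusion.** The point holds in a limited form. The only numeric acceptability criterion is labelled for participants and the Bundle, but the instruments listed can measure only nurses' satisfaction with the online course and the workshop. At most about 48 of 110 to 122 planned intervention staff, 39% to 44%, can contribute (36% to 48% over the range of PCW splits). PCWs, managers, the PCW course, the toolkit and the coaching fall outside the percentage.

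This rests on Table 1 being the full list of instruments, on recruitment at the planned numbers, and on the assumed PCW split. It does not show that acceptability as a whole ignores these groups, or that the threshold is biased towards passing.

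**What to change.** Add one satisfaction item, for intervention sites only, to contacts that already take place:

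- PCWs: with the KCS-PCW after their online course.
- Managers/senior leaders: with the t2 audit, covering the toolkit and the coaching.
- Nurses: with the KCS-Nurse at t2, covering the coaching.

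Report the percentage satisfied for each staff group, with the number responding out of the number enrolled. A separate 75% pass/fail test for each group is not advisable. With 12 to 24 managers, the 95% half-width at 75% is 1.96 × √(0.1875/12) = 25 points down to 1.96 × √(0.1875/24) = 17 points, before any allowance for clustering. Nor is it necessary to count non-response as dissatisfaction, since the response count lets the reader judge.

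If no item can be added, restate the Table 3 criterion as 75% or more of responding nurses satisfied with the online course and workshop. Limit the progression conclusion to that, and rest acceptability to PCWs and managers explicitly on the interviews and, for managers, the audit.

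The cost is a slightly longer survey, a change of table wording, and possibly a lower reported percentage. The minimum version costs only the wording.

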**Table 2 Tab2:**
[figure not shown]
Timeline of study procedures, including enrolment, interventions, and assessment points

**Table 3 Tab3:** Criteria, data collection methods, and thresholds for progression to a definitive trial

Criteria	Data collection	Threshold
(ii) Acceptability of the bundle	• Feedback surveys • Audit tool • Qualitative interviews	• 75% + participants “satisfied” or “very satisfied” • Thematic analysis of qualitative interviews • Descriptive analysis of audit tool
(iii) Fidelity of implementation	• Participant completion and withdrawal record • KCS-Nurse • KCS-PCW • NPC-Scale-SF • Clinical data extraction form	• Site retention: 20 sites complete all trial phases • Participant retention: ≥ 80% of enrolled participants complete all study follow-ups (t_0_, t_1_, t_2_) • Fidelity to data collection: 75% of all *expected* data points collected across KCS-Nurse, KCS-PCW, NPC-Scale-SF, and Clinical Data Extraction Forms from sites and participants who complete all trial phases • Internal Consistency of KCS-Nurse: Achieves acceptable internal consistency
(iv) Compatibility of bundle with standard practice	• Qualitative interviews • Audit tool	• Thematic analysis of qualitative interviews • Descriptive analysis of audit tool

Prior to site randomisation, information will be collected from organisations on their size, ownership and staffing, and from individual nurses and PCWs in terms of their qualifications, years in nursing and in working in residential aged care. The research team will provide sites with extraction forms to obtain key information from the medical records of residents with IDCs who consent to participate in the study. Research staff will be trained in obtaining informed consent and in the use of the extraction forms prior to inviting residents to participate. We anticipate some participating nurses may complete the online course but will be unable to complete a workshop due to workshop capacity limitations. These nurses will be flagged, and their outcome data will not be combined with workshop participants’ data.

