### Feasibility cRCT

This is a multi-centre, facility-level cluster randomised control feasibility trial with an embedded process evaluation conducted in residential aged care homes in Australia. After baseline data are collected for all outcome measures, 12 aged care homes will be randomised to receive the intervention and 12 will continue to provide usual practice (control). Each cluster comprises one site (residential aged care home). The control sites are included to assess acceptability of randomisation and fidelity to data collection and to provide a comparator for pilot data. Control sites will receive some elements of the *Bundle* after the trial closes and data collection is completed at their site. Figure 1 provides an overview of the trial.

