### Participant inclusion/exclusion criteria

#### Nurses

We aim to recruit at least four nurses (RNs and ENs) per site (96 total), as the face-to-face component of the training will be delivered to groups of four. Inclusion criteria require participants to be employed at an enrolled site (permanent or casual); registered to practice in Australia as an EN or RN with the Nursing and Midwifery Board of Australia; are planning to remain employed at the site for the trial period. Exclusion criteria are as follows: the nurse cannot commit to completing the online course about person-centred IDC care and/or attend the Catheterisation Skills Workshops.

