#### Personal care workers

We aim to recruit 100 PCWs across intervention and control sites. Inclusion criterion is that the participant plans to be employed at the site during the trial period.

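### The pooled 75% data-collection threshold can be met with no follow-up clinical data, because no instrument has its own minimum

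*Protocol article*

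**What the plan says.** The Primary outcome section of the protocol article says that the feasibility of a definitive trial is judged against the progression criteria in Table 3. Under fidelity of implementation, that table asks for 75% of all expected data points "collected across KCS-Nurse, KCS-PCW, NPC-Scale-SF, and Clinical Data Extraction Forms from sites and participants who complete all trial phases". This is one figure over four instruments, and none has a floor of its own.

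The same cell holds separate retention criteria: "Site retention: 20 sites complete all trial phases", and at least 80% "of enrolled participants complete all study follow-ups" at t0, t1 and t2.

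Table 1 gives the schedules. KCS-Nurse (51 items) and KCS-PCW (34 items) are taken at t0, t1 and t2. The NPC Scale-SF (35 items) is taken at t1. The Clinical Data Extraction Form is taken at t0 and t1 in both arms. Of these four, only the last records IDC-related complications and hospital or emergency admissions. Baseline is collected before randomisation (Feasibility cRCT section), so the t1 form is the only one carrying clinical data from after allocation.

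The Feasibility cRCT section also gives data collection as a reason for having a control arm: "The control sites are included to assess acceptability of randomisation and fidelity to data collection and to provide a comparator for pilot data".

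**The concern.** A progression criterion for data collection should show whether the data a definitive trial needs can be obtained in this setting. The Secondary outcomes section says these outcomes include data likely to be used in that trial, and complication rates are among them. Those rates depend on managers or registered nurses at each home completing an extraction form, and the Background itself lists staff shortages and under-resourcing as barriers to research in aged care homes.

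Pooling that form with three staff questionnaires lets good survey return offset failed clinical extraction. At stake is a decision to proceed that reports the data-collection criterion as met while little or no post-baseline complication data exist.

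**Working it through.** **The plan's own figures.** The 75% threshold comes with no derivation. The only computed figure is the 62 nurses in the Sample size calculation section, and it reproduces: 1.96² × 0.80 × 0.20 / 0.10² = 61.5, rounded up to 62. It has no bearing on the pooled threshold.

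**Inputs.** 24 homes, a target of 96 nurses and 100 PCWs, and the schedules and item counts in Table 1. Not stated, and therefore assumed: R, the consenting residents per site (1 to 10); the number of fields on the clinical form (10 to 20); and whether a data point is a form or an item. As a guide to R, the Background's 8.4% gives about 5 residents in a home of 60, 6.7 in a home of 80 and 8 in a home of 100, before consent. Site eligibility requires only one.

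**Expected forms.**
- KCS-Nurse: 96 × 3 = 288
- KCS-PCW: 100 × 3 = 300
- NPC Scale-SF: 96 × 1 = 96
- Staff total: 684
- Clinical: 24 × 2 × R = 48R, half at t0 and half at t1

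**Staff forms complete, t0 clinical forms in hand, every t1 clinical form missing.** The criterion is met when (684 + 24R) / (684 + 48R) ≥ 0.75. That gives 171 ≥ 12R, so R ≤ 14.25. The pooled rate is 96.7% at R = 1, 89.0% at R = 4, 82.0% at R = 8 and 79.4% at R = 10. At 8.4% prevalence and full consent, R = 14.25 would need an average home of about 14.25 / 0.084 = 170 residents.

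**Staff forms complete, no clinical form at all.** The criterion is met when 684 / (684 + 48R) ≥ 0.75, so R ≤ 4.75. The pooled rate is 93.4% at R = 1, 78.1% at R = 4, 74.0% at R = 5 and 64.0% at R = 8.

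**Counting items instead.** Staff items are 51 × 288 + 34 × 300 + 35 × 96 = 14,688 + 10,200 + 3,360 = 28,248. With f fields on the clinical form, no clinical data at all still passes when 28,248 / (28,248 + 48Rf) ≥ 0.75, so Rf ≤ 196.2. That is R up to 19.6 with 10 fields and 9.8 with 20 fields.

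**Incomplete staff return, counting forms.** Take R of about 6.7, which is 24 × 80 × 8.4% ≈ 161 residents and 322 clinical forms. The total is 684 + 322 = 1,006 forms, and 75% of that is 754.5.
- 100% staff return: (754.5 − 684) / 322 = 22% of clinical forms needed
- 90%: (754.5 − 615.6) / 322 = 43%
- 85%: (754.5 − 581.4) / 322 = 54%

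The t0 forms supply 50%, which is enough in the first two cases and just short in the third. In general, with staff return s, t0 forms alone suffice up to R = 684(s − 0.75) / 12. That is 14.25 at s = 1, 8.55 at 0.90 and 5.7 at 0.85.

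**Completers only, at minimum retention.** With 20 sites, 77 nurses and 80 PCWs there are 231 + 240 + 77 = 548 staff forms and 40R clinical forms. The limits become R = 13.7 (no t1 clinical forms) and R = 4.57 (no clinical forms), so the result hardly moves.

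**Other thresholds.** The completion record counts "Number of nurses and PCWs who enrol, complete or withdraw from the education or application to practice phase", and the Residents section says residents complete no measures. No other Table 3 threshold tests clinical-form completeness separately.

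**The case against.** **Attrition.** Because the denominator holds only completers, a reader might infer that dropout is ignored and that the criterion is close to self-fulfilling, with completers near 100% by construction. The protocol does not support this. Retention of sites and of participants has its own thresholds in the same cell, and measuring retention and completeness separately is a defensible choice. Completing all trial phases need not mean completing all follow-ups: the Intervention section names the phases as education and application to practice, so a participant could finish both and still miss questionnaires.

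A reader might also multiply 0.80 by 0.75 and conclude that only 60% of planned data is needed. That credits dropouts with nothing, although baseline precedes randomisation. With 161 residents, t0 accounts for (96 + 100 + 161) / 1,006 = 35.5% of forms. Crediting this to the 20% who leave gives about 0.60 + 0.20 × 0.355 = 67%.

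**Zero clinical data.** A reader might infer that the criterion always passes with no clinical data at all. Counting forms with 161 residents, that case scores 684 / 1,006 = 68% and fails. The claim holds only at smaller R, or when items are counted. The results with high staff return are also the favourable end, as the 85% case shows.

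**Role of the clinical data.** Complication rates are descriptive pilot data here, and the article does not name them as the primary outcome of a definitive trial. Interviews and the process evaluation might reveal an extraction problem. This limits the consequence but does not supply a threshold.

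**Left to other documents.** Completeness tables by instrument, and the meaning of an expected data point, may well sit in a fuller document. The pooled threshold itself is stated here. If site completion were defined to require the t1 clinical forms, the gap would largely close, but the article does not say so.

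**Conclusion.** The concern holds for pooling. As written, the criterion can be met with no post-baseline clinical data. Counting forms, with staff forms complete and t0 clinical forms in hand, this is so across the whole assumed range of 1 to 10 consenting residents per site, and up to 14.25. It can be met with no clinical data whatever up to 4.75 per site counting forms, or about 10 to 20 counting items. The margin shrinks as staff return falls: at R of about 6.7, t0 forms still carry the criterion at 90% staff return but not quite at 85%.

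These figures assume the recruitment targets are met, and they rest on assumed values of R and of the number of clinical fields. The conclusion does not extend to the completers-only denominator or to the retention thresholds, which are acceptable as they stand.

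**What to change.** In Table 3, apply the 75% threshold separately to each instrument at each timepoint. At minimum, require the t1 Clinical Data Extraction Form to reach 75% on its own. Count expected clinical forms for consenting residents, ending at death or discharge. With no deaths or discharges, 24R forms are then expected at t1 and 18R needed: 96 and 72 at R = 4, or 192 and 144 at R = 8.

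Keep the retention thresholds and the completers-only denominator. Report completeness among all enrolled sites and participants alongside, as a descriptive figure.

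The cost is slightly more tabulation and a criterion that is harder to meet. The full version has nine instrument-by-timepoint figures to pass (3 + 3 + 1 + 2); the minimum version adds one. The reported result may look less favourable than the pooled figure.

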#### The catheterisation skills workshop for nurses

The catheterisation skills workshop has been designed for nurses by CHA and will be delivered by facilitators who are advanced practice nurses who have advanced clinical skills or knowledge in continence or urology nursing. The workshop includes practice of indwelling catheterisation insertion on both male and female manikins as well as changing a suprapubic catheter. Workshop facilitators use a comprehensive checklist to assess learners and provide feedback on areas for development to each learner, based on their performance. The workshops will be conducted either on-site or at a nearby alternative venue if required. The number of nurses able to attend each workshop is limited to four due to the intensity of the program.

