### Comparator

Sites assigned to the control arm will continue with usual care during the trial period. After data collection is complete at their site, they will be given access to all the resources of the *Bundle* except the Catheterisation Skills Workshops for nurses about catheter insertion. If they wish to complete the workshop after the research has been concluded, they will be referred to CHA to discuss their individual needs.

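### Keeping online-only nurses' outcome data apart from workshop attendees' leaves no as-randomised KCS-Nurse summary for the intervention arm

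*Protocol article*

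**What the plan says.** The rule stands in the Protocol article under Outcome measures, Primary outcome, in the paragraph after Table 3. The authors anticipate that "some participating nurses may complete the online course but will be unable to complete a workshop due to workshop capacity limitations", and continue: "These nurses will be flagged, and their outcome data will not be combined with workshop participants" (the sentence ends with the word for data).

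Other sections bear on it:

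- **Participant inclusion/exclusion criteria, Nurses:** "We aim to recruit at least four nurses (RNs and ENs) per site (96 total"). This sets a minimum per home and no maximum.
- **The catheterisation skills workshop for nurses:** "The number of nurses able to attend each workshop is limited to four due to the intensity of the program".
- **Feasibility cRCT:** "After baseline data are collected for all outcome measures, 12 aged care homes will be randomised to receive the intervention". One stated purpose of the control homes is "to provide a comparator for pilot data".
- **Comparator:** "Sites assigned to the control arm will continue with usual care during the trial period". They have no workshop in that time.
- **KCS-Nurse and Secondary outcomes:** every participating nurse completes the scale at t0, t1 and t2, and it supplies pilot data on what the Bundle does to nurses' knowledge and confidence.
- **Data analysis:** scale scores are summarised descriptively. Nothing there restores a summary of all intervention nurses or says which intervention group is shown against controls.

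**The concern.** Homes are randomised, so the comparison that randomisation protects is all enrolled nurses in intervention homes against all enrolled nurses in control homes. The rule divides one side of that comparison by something that happens after allocation and cannot happen on the other side. A control nurse who would have missed a place remains in the control group; her counterpart in an intervention home is moved to a separate group.

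The protocol does not say how places are given out. If they go to keener, more experienced, less experienced or more conveniently rostered nurses, the two intervention subgroups differ for reasons other than the workshop. The KCS-Nurse levels, spread and change by arm would carry that difference into the planning of a definitive trial. The same section of the protocol that defines the secondary outcomes describes them as data likely to be used in such a trial.

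This is a rule the protocol states, so it is not a detail left open for a statistical analysis plan. A plan that obeyed it could not report the whole intervention arm.

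**Working it through.** **The plan's own figures.** The nurse target is 24 homes x 4 = 96, which matches the protocol. The required sample of 62 also reproduces: 1.96² x 0.80 x 0.20 / 0.10² = 61.46, rounded up to 62. The present point depends on neither figure, and the fix changes neither.

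**Order of events.** Baseline is collected, homes are randomised, then workshops are held in intervention homes only. The grouping variable therefore follows randomisation and exists in one arm.

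**Size of the shift.** Let f be the share of intervention nurses without a place. Let A and N be the mean scores that attendees and online-only nurses would have had without the workshop, and let D = A - N in SD units. The whole-arm mean is (1 - f)A + fN. Then:

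- attendees minus whole arm = A - [(1 - f)A + fN] = f x D
- online-only minus whole arm = -(1 - f) x D

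**Inputs.** Four places per workshop and 12 intervention homes come from the protocol. One workshop per home, the number of nurses per home, and D are assumptions. Under them there are 12 x 4 = 48 places.

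| Nurses per intervention home | Enrolled | Without a place | f | f x D, D = 0.2 | D = 0.5 | D = 0.8 |
|---|---|---|---|---|---|---|
| 4 | 48 | 0 | 0 | 0 | 0 | 0 |
| 5 | 60 | 12 | 0.20 | 0.04 | 0.10 | 0.16 |
| 6 | 72 | 24 | 0.33 | 0.07 | 0.17 | 0.27 |

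A negative D reverses the sign. The shift is zero when f = 0 or D = 0.

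**How these shares relate to the target.** Five or six nurses in all 24 homes would be 120 or 144 nurses, which is 25% or 50% above 96. At exactly four per home and one workshop each, nobody lacks a place.

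**After the change.** With every enrolled nurse kept in the arm of her home, no one is removed and the selection shift is zero.

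**The case against.** The strongest reply is that the rule separates data and does not discard them. Both subgroups can be reported, and showing nurses who received the full Bundle apart from those who had only the online course is reasonable when studying delivery. This stands as a reason to keep the split as a supplement. It does not supply the missing summary. A whole-arm mean could be rebuilt from two subgroup means and counts, but the protocol's default summary for all subscales is the median with quartiles, and those cannot be rebuilt that way.

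A second reply is that little rests on the comparison. This is true: the primary outcome is feasibility, the analysis is descriptive, and no threshold in Table 3 uses a KCS-Nurse difference between arms.

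A third is that the target of 96 is exactly four per home, and that nurses are excluded at enrolment if "the nurse cannot commit to completing the online course about person-centred IDC care and/or attend the Catheterisation Skills Workshops". The first part limits how many nurses may be affected, although the protocol itself expects some to miss out and the Sample size calculation section allows for uneven cluster sizes. The second part concerns willingness and applies to both arms; the shortfall here is one of capacity.

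Baseline KCS-Nurse scores will also show part of any difference between the subgroups, but not differences in motivation or roster.

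A reader might infer more than the text supports:

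- **That online-only nurses are dropped.** The text only keeps them apart.
- **That attendees against all controls is the planned contrast.** No group is named.
- **That the pilot effect would be overstated.** How places are allocated is not stated, so the direction is unknown.
- **That homes will always have more nurses than places.** The text says only that some nurses may be affected, and the number of workshops per home is not given.

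**Conclusion.** The point holds in a limited form. The no-combining rule conditions on an event that follows randomisation and can occur only in the intervention arm. As written it leaves no as-randomised KCS-Nurse summary of that arm, and neither intervention subgroup set beside the undivided controls is the randomised comparison.

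The document fixes neither the size nor the direction of any bias. The illustrative shift for attendees is 0.04 to 0.27 SD in either direction. It rests on one workshop of four per home, five or six nurses per home (more than the target implies) and an assumed difference of 0.2 to 0.8 SD. At four nurses per home, or with places unrelated to outcome, it is zero.

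The consequence is confined to the pilot data and what is later planned from them. No confirmatory test or progression decision in the protocol depends on it.

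**What to change.** Replace the no-combining sentence with text to this effect: *The main KCS-Nurse summary at t0, t1 and t2 will include all enrolled nurses in the arm to which their home was randomised, regardless of workshop attendance. Within the intervention arm, workshop attendees and nurses who completed only the online course will also be reported separately as a supplementary split.*

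The cost is one sentence. The data are already collected from every participating nurse, and the figures of 62 and 96 do not change. The downside is that the as-randomised difference may look smaller, because it mixes full and partial exposure to the Bundle; the supplementary split lets readers see this.

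If a workshop-specific contrast is also wanted, homes in both arms could nominate their workshop nurses at baseline, before randomisation. That is an optional design addition. A workshop-specific effect is not among the five objectives, and the correction does not depend on it.
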